### Sample size calculations

Our sample size of 88 ensures adequate power to detect significant changes in the peak knee adduction moment after 12 weeks. We estimate a change in the peak knee adduction moment after a strengthening program to be between 5 and 10%. Based on our participants with knee OA from previous studies, a 7.5% reduction equates to an absolute change of approximately 0.3 Nm/BW*HT %. Estimates of the standard deviation of change scores are 0.4 Nm/BW*HT % based on data obtained from ongoing studies in our laboratory investigating conservative treatment for knee OA as well as other published reports [41]. Thus, a total of 38 patients per group are required to detect a 0.3 Nm/BW*ht % change with 90% power (2 sided test, alpha = 0.05). We also assume an attrition rate of approximately 15% for the duration of the study, suggesting that 44 patients per group will be required.

### Statistical analysis

Data will be assessed in a blinded fashion. All analyses will be conducted on an intention-to-treat principle using all randomised participants. Missing data will be replaced by the last score carried forward. Demographic characteristics and baseline data will be summarised by descriptive statistics. For outcomes measured on a continuous scale, differences in mean change from baseline to 12 weeks between groups will be evaluated using linear regression modelling while adjusting for baseline levels of the outcome measure. For the knee adduction moment, gait speed, disease severity (KL grade), and pain will also be included as covariates. Model assumptions will be checked by standard diagnostic plots [42]. Participant rating of perceived change will be compared between the two groups by calculating the relative risks and their 95% confidence intervals using log binomial regression [43].

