**Methods/Design:**

88 participants with painful, radiographically confirmed medial compartment knee OA and varus alignment will be recruited from the community and randomly allocated to a hip strengthening or control group using concealed allocation stratified by disease severity. The hip strengthening group will perform 6 exercises to strengthen the hip abductor and adductor muscles at home 5 times per week for 12 weeks. They will consult with a physiotherapist on 7 occasions to be taught the exercises and progress exercise resistance. The control group will be requested to continue with their usual care. Blinded follow up assessment will be conducted at 12 weeks after randomisation. The primary outcome measure is the change in the peak external knee adduction moment measured during walking. Questionnaires will assess changes in pain and physical function as well as overall perceived rating of change. An intention-to-treat analysis will be performed using linear regression modelling and adjusting for baseline outcome values and other demographic characteristics.

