### Outcome assessment

Participants will be assessed at baseline and at 12 weeks by an assessor blinded to group allocation. Age, gender, duration of knee OA symptoms, previous treatment, surgery and medication use for knee OA will be obtained at the baseline assessment. Radiographic disease severity will be assessed from the baseline x-ray using the Kellgren and Lawrence grading system [30]. Skyline knee x-rays performed in nonweightbearing at 20° knee flexion will also be obtained to assess severity of OA within the patellofemoral joint. X-rays will be evaluated according to osteophytes and joint space narrowing based on a 4 point scale [33].

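### With one follow-up visit, carrying the last score forward records zero change for every dropout, which biases the treatment difference unless dropouts are truly unchanged on average or the errors cancel between arms

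*Protocol article*

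**What the plan says.** The Statistical analysis section of the protocol article gives one rule for missing values, without exception: "Missing data will be replaced by the last score carried forward". It also says "All analyses will be conducted on an intention-to-treat principle using all randomised participants". For continuous outcomes, "differences in mean change from baseline to 12 weeks between groups will be evaluated using linear regression modelling", with adjustment for the baseline value.

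The Outcome assessment section sets two measurement times: "Participants will be assessed at baseline and at 12 weeks by an assessor blinded to group allocation". The abstract agrees: "Blinded follow up assessment will be conducted at 12 weeks after randomisation". The physiotherapy visits between these times (Hip strengthening group) are for teaching and progressing the exercises. No outcome is listed at them, and the control group has no such visits. Perceived change is collected once, at the end of the study (Table 2, Symptoms).

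The Sample size calculations section anticipates losses: "We also assume an attrition rate of approximately 15% for the duration of the study".

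**The concern.** With two assessments, anyone who misses week 12 has only a baseline score to carry. The analysed quantity is change from baseline, so that person's change becomes zero by construction. The rule thus assumes that every dropout is unchanged, and nothing in the article supports this.

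The size and interval of the primary result, the change in peak knee adduction moment, are at stake, and so are the secondary pain and function results. The direction of the error is not fixed. Equal loss with a real benefit shrinks the effect. Unequal loss with a change common to both arms can produce a difference where none exists. Unequal loss is conceivable, since one arm exercises five times a week and the other continues usual care, but the article gives no figures for it.

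For perceived change the rule has nothing to work with: there is no earlier rating.

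This is a stated method, not a detail left to a fuller document. A fuller plan could add sensitivity analyses, but the stated rule would still govern the main result.

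**Working it through.** **Inputs from the Sample size calculations section.** Effect: "a 7.5% reduction equates to an absolute change of approximately 0.3 Nm/BW*HT" (in % units). Spread: "Estimates of the standard deviation of change scores are 0.4 Nm/BW*HT" (same units). Two-sided alpha 0.05, 90% power, 38 per group, 44 per group after 15% attrition.

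**Assumptions, not in the article.** Dropout is unrelated to outcome, and dropouts would have changed as completers did. The simulation baseline has mean 4 (0.3/0.075) and SD 0.9. Unequal dropout rates and shared changes are illustrative.

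**1. The plan's own figure.** n = 2(1.960 + 1.282)² × (0.4/0.3)² = 2 × 10.51 × 1.778 = 37.4, so 38 per group, as stated. Attrition: 38 × 1.15 = 43.7, so 44, as stated (38/0.85 = 44.7 would give 45; this does not matter here). Expected completers are 44 × 0.85 = 37.4 per group.

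**2. What the rule does.** Change = week 12 − baseline. With week 12 replaced by baseline, change = 0. Number affected: 0.15 × 88 = 13.2.

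**3. Expected result at equal 15% loss.** With loss d, true mean change μ and SD σ, an arm has mean (1 − d)μ and variance (1 − d)σ² + d(1 − d)μ².

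- Estimate: 0.85 × 0.30 = 0.255.
- Variance, exercise: 0.85 × 0.16 + 0.15 × 0.85 × 0.09 = 0.1475. Control: 0.85 × 0.16 = 0.1360.
- SE under the rule: √[(0.1475 + 0.1360)/44] = 0.080.
- SE from observed data: √(2 × 0.16/37.4) = 0.0925. The simulated model SE is 0.093, so the rule's SE is about 14% smaller (0.080/0.093 = 0.86).
- Coverage: the centre is off by 0.045/0.080 = 0.56 SE, so coverage ≈ Φ(1.40) − Φ(−2.52) = 0.919 − 0.006 = 0.913.

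**4. Simulation** (8,000 trials per row, 44 per arm, baseline-adjusted regression; negative values favour exercise):

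| Loss, exercise/control | True mean change, exercise/control | Carried forward: estimate, coverage, rejection | Observed data: estimate, coverage, rejection |
|---|---|---|---|
| 15%/15% | −0.30/0 | −0.253, 90.9%, 87.7% | −0.299, 94.9%, 88.5% |
| 15%/15% | 0/0 | −0.001, 95.0%, 5.0% | −0.001, 95.0%, 5.0% |
| 25%/5% | −0.30/0 | −0.226, 85.6%, 79.2% | −0.301, 95.1%, 89.1% |
| 25%/5% | +0.20/+0.20 | −0.040, 91.7%, 8.3% | 0.000, 94.5%, 5.5% |
| 25%/5% | −0.20/−0.20 | +0.041, 91.8%, 8.2% | +0.001, 95.4%, 4.6% |

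The false difference in the fourth row follows directly: 0.75 × 0.20 − 0.95 × 0.20 = −0.04.

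**5. Source of the lost coverage.** In the first row the model SE under the rule is 0.080 and the actual spread of that estimator is 0.081. The SE therefore describes its own estimator well, and coverage is lost mainly because the interval is centred in the wrong place.

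**The case against.** The strongest reply is that the bias depends on what dropouts would have done, which the article cannot settle. Suppose their true change is zero, which is plausible for people who stop exercising and for a load measure in untreated controls. The true difference over all randomised participants is then 0.85 × 0.30 = 0.255. In simulation the rule is then unbiased (0.255, coverage 95.1%), while observed-data regression overstates the effect (0.300, coverage 92.6%). This stands, and it is why the point is conditional.

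The documents do not support some stronger readings that a reader might infer:

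- *That the effect is certainly biased.* It is not if dropouts are unchanged on average or the errors cancel. With no change in either arm, type I error stays at 5.0%.
- *That the interval fails because imputed zeros make the residual SD too small.* The SE matches the estimator's own spread. It is smaller than the observed data justify, but the shifted centre causes most of the lost coverage.
- *That the trial loses power at its planned attrition.* At equal 15% loss, power is 88% against 89% on observed data. A clear gap needs unequal loss, which the article does not give.
- *That a missing-at-random analysis would correct for someone who leaves with a pain flare.* It would give that person roughly the arm's average response, which may be more favourable than zero. Only a delta-adjusted analysis addresses this case. Stopping exercise is also not the same as missing week 12.

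What survives is that the plan builds one untested assumption about dropouts into the main analysis and treats the imputed values as observed.

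**Conclusion.** The concern holds in conditional form. It is certain from the design that every missing week-12 score on a continuous outcome becomes a change of zero, and that perceived change has no score to carry.

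The size of the harm rests on assumptions. If dropouts would have responded like completers, equal 15% loss removes 0.045 of 0.30. That is a little over half of the rule's own SE, and it lowers coverage to about 91% with little effect on power. At an assumed 25%/5% loss the estimate falls to about 0.225. With no true difference but a shared change of 0.2, the same loss gives a false difference of about 0.04 and a type I error of about 8%. The sign of that error depends on the direction of the shared change, so the rule cannot be defended as reliably conservative.

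**What to change.** Replace the sentence on missing data in the Statistical analysis section with the following elements:

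- **Primary analysis:** the same baseline-adjusted regression under missing-at-random, using either observed week-12 data or multiple imputation within arm from baseline knee adduction moment, gait speed, KL grade and pain. Other week-12 outcomes add little to the imputation, because someone who misses the visit will generally lack them all. If observed data are used, reword the statement that all randomised participants are analysed.
- **Follow-up:** state that all randomised participants are sought for the week-12 assessment whether or not they still exercise.
- **Sensitivity analyses:** keep zero-change imputation, labelled as such, beside a delta-adjusted analysis that covers dropouts who worsened.
- **Perceived change:** analyse observed ratings, or state how missing ratings are imputed.

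The cost is new wording and a little programming. Standard errors will be wider (about 0.093 instead of 0.080 at the planned attrition), which reflects the information actually held.

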## Methods/Design

### Design

This will be a single-blind randomised controlled trial (Figure 1). Potential participants will undergo telephone screening followed by clinical examination by a physiotherapist to ensure eligibility. A screening x-ray will be performed to quantify knee joint alignment and assess disease severity. Eligible participants will then be stratified by disease severity (Kellgren and Lawrence grade 2, 3 and 4) [30] and randomly allocated in permuted blocks of 4 to 6 to hip strengthening or control groups. The randomisation sequence will be generated *a priori *using the random number function in Excel by an independent investigator not directly involved in assessment of participants. Allocation will be sealed in opaque and consecutively numbered envelopes held in a central location. These will be opened in sequence by a person not involved in the study after recruitment and baseline testing of participants.

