### Participants

88 men and women (approximately 30 each of KL grades 2, 3, and 4) aged over 50 years will be recruited from the community via advertisements in local clubs, libraries, and the print and radio media in metropolitan Melbourne, Australia and from our database of people who have registered their interest in participating in research studies. Eligibility will be confirmed by radiographic and clinical examination. People with tibiofemoral joint OA fulfilling American College of Rheumatology classification criteria [31] and reporting average knee pain on walking >3 on an 11-point scale (0 = no pain; 10 = maximal pain) will be included. Other inclusion criteria will be: (i) knee alignment ≤ 182° on a standardised semiflexed standing posteroanterior knee x-ray (which corresponds to a mechanical axis angle of ≤ 180° on a full leg x-ray, indicating varus alignment) [32]; (ii) predominance of pain/tenderness over the medial region of the knee and; (iii) medial compartment radiographic OA defined as at least Grade 1 medial joint space narrowing or Grade 1 medial tibial or femoral osteophytes [33].

Exclusion criteria will include: (i) questionable radiographic knee OA (Kellgren and Lawrence Grade 1 [30]); (ii) lateral tibiofemoral joint space width less than medial; (iii) symptoms originating predominantly from the patellofemoral joint as determined by clinical examination; (iv) knee surgery or intra-articular corticosteroid injection within 6 months; (v) current or past (within 4 weeks) oral corticosteroid use; (vi) systemic arthritic conditions; (vii) history of hip or tibiofemoral/patellofemoral joint replacement or tibial osteotomy; (viii) any other muscular, joint or neurological condition affecting lower limb function; (ix) planning to commence exercise or other treatment for knee OA in the next 12 months; (x) unable to ambulate without a gait aid and; (xi) non-English speaking.

Ethical approval has been obtained from the University of Melbourne Human Research Ethics Committee (HREC No. 0709220) and from the Department of Human Services Victoria, Radiation Safety Committee. All participants will provide written informed consent.

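### Randomisation is stratified by KL grade, but the linear models for the secondary continuous outcomes leave KL grade out, so their standard errors may be reported too wide

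*Protocol article*

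**What the plan says.** The Design section of the protocol article has eligible participants "stratified by disease severity (Kellgren and Lawrence grade 2, 3 and 4", then "randomly allocated in permuted blocks of 4 to 6 to hip strengthening or control groups". The Participants section plans for "88 men and women (approximately 30 each of KL grades 2, 3, and 4", so the three strata are of similar size.

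The Statistical analysis section gives one model for outcomes on a continuous scale: the between-group difference in mean change is "evaluated using linear regression modelling while adjusting for baseline levels of the outcome measure". It then makes one addition: "For the knee adduction moment, gait speed, disease severity (KL grade), and pain will also be included as covariates". No such addition is made for any other continuous outcome. By the list of measures in Table 2, those are the peak hip adduction moment, pelvic obliquity and trunk lean, muscle strength, the pain and restriction scales, the WOMAC, the step test and the stair task.

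The abstract describes the analysis as "adjusting for baseline outcome values and other demographic characteristics". That wording does not name KL grade, and it does not match the covariates listed under Statistical analysis.

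**The concern.** Stratifying by KL grade makes the arms nearly equal in KL grade. If KL grade is prognostic, this removes part of the chance variation in the treatment comparison. A model without KL grade keeps that variation in its residual, so the reported standard error describes a less precise trial than the one that was run. Intervals are then wider than they need be, and the test rejects less often than its nominal level.

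The second hypothesis, on pain and physical function, rests on the secondary outcomes. The sample size was set for the knee adduction moment alone, so the article claims no power for pain or function, and precision there is worth keeping. The Discussion gives a general reason to take KL grade seriously: gait biomechanics may depend on it. That reason reaches the hip adduction moment, pelvic obliquity and trunk lean as well as the knee adduction moment, yet only the last is adjusted for KL grade.

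**Working it through.** **The plan's own figure.** Inputs from Sample size calculations: difference 0.3, SD of change 0.4, two-sided alpha 0.05, power 90%. n per group = 2 × (1.960 + 1.282)² × (0.4/0.3)² = 37.4, rounded up to 38, as stated. For attrition of 15%, 38 × 1.15 = 43.7, giving the stated 44 (38/0.85 = 44.7 would give 45). This calculation concerns the knee adduction moment, whose model already contains KL grade, so nothing below changes it.

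**Inputs for the check.** From the article: 88 participants, two arms of 44, three strata of about 30, blocks of 4 to 6. Assumed, because the article gives no figure: R², the share of outcome variance that KL grade explains after the baseline value is accounted for, from 0 to 0.20; and an effect of 0.6 SD, with the total SD (after baseline) fixed at 1.

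**Formulas.** With arms balanced within strata:

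- True SE of the treatment estimate, with or without KL grade in the model: (2/√88) × √(1 − R²).
- Reported SE without KL grade: about 2/√88 = 0.213.
- Ratio of reported to true SE: 1/√(1 − R²).
- True type I error without KL grade: the two-sided tail of t on 85 degrees of freedom (88 less intercept, treatment and baseline) beyond 1.988/√(1 − R²).

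**Numbers put in.** At R² = 0.20 the true SE is 0.213 × √0.80 = 0.191, the ratio is 1/√0.80 = 1.118, and the critical value becomes 1.988 × 1.118 = 2.223, whose two-sided tail is 2.9%.

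**Simulation.** 6,000 trials per setting, strata of 30/29/29, blocks of 4 or 6, linear regression with treatment and a baseline covariate, with and without two KL indicators. The simulated baseline was unrelated to outcome, so R² is directly what KL grade adds beyond it.

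| R² (assumed) | SE too wide by (formula) | Type I error without KL: formula | Type I error without KL: simulated | Power at 0.6 SD, without / with KL | Gap (points) |
|---|---|---|---|---|---|
| 0 | 0% | 5.0% | 4.6% | 78.5 / 78.5% | 0 |
| 0.02 | 1.0% | 4.8% | 4.3% | 80.0 / 80.1% | 0.1 |
| 0.05 | 2.6% | 4.4% | 4.1% | 79.1 / 80.3% | 1.2 |
| 0.10 | 5.4% | 3.9% | 4.3% | 80.3 / 83.1% | 2.8 |
| 0.20 | 11.8% | 2.9% | 2.8% | 81.5 / 87.4% | 5.9 |

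Monte Carlo error on a 5% rate is √(0.05 × 0.95/6000) = 0.28 points, so simulation and formula agree within noise. With KL grade in the model the simulated type I error lay between 4.3% and 5.2% over these settings.

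At R² = 0.20 the estimate itself varied almost equally in both analyses (empirical SE 0.190 without KL grade, 0.189 with it), while the average reported SE was 0.215 against 0.192. What is lost is credit for precision that the design has already bought. At R² = 0 the ratio of reported SE without to with KL grade was 0.999, so including KL grade needlessly costs next to nothing.

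**The case against.** The strongest objection is that the loss is conditional. It arises only if KL grade predicts an outcome beyond that outcome's own baseline value, which is already in the model. The article gives no figure linking KL grade to pain, function or strength, and its stated rationale is about gait. This stands: the cost may be nil, and an R² of 0.02 makes it about 1% of the standard error. A reader might infer that every secondary analysis loses precision; the article does not support so flat a statement.

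The error is also on the safe side, with neither bias nor inflated type I error. That stands too, and it keeps the point minor.

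Two further inferences are tempting. One is that power falls to about 72% at R² = 0.20. That figure appears only if KL variance is added on top of a fixed within-stratum SD. The total SD then grows to 1/√0.80 = 1.118, and the effect shrinks to 0.6/1.118 = 0.54 of it. With total SD fixed, power without KL grade does not fall; it is merely lower than it would be with KL grade included. The other is that the perceived-change analysis, "calculating the relative risks and their 95% confidence intervals using log binomial regression", has the same fault. No covariates are named there, but none are excluded, and a precision gain from adjustment was not shown for that model.

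It could be said, finally, that a condensed article leaves covariates to the analysis plan. Here the article does list them and reserves KL grade for one outcome, so the objection does not remove the mismatch.

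**Conclusion.** The mismatch is real and minor. As written, the linear models for pain, function, strength and the secondary gait measures omit the factor on which randomisation is stratified. For an assumed R² of 0 to 0.20, the reported standard errors are too wide by 0% to about 12%, type I error is between 5% and about 3%, and power is about 0 to 6 points below what the same trial would have with KL grade in the model. The power figures also rest on an assumed 0.6 SD effect with total SD fixed. The treatment estimates are unbiased. The primary analysis and the sample size stand, and the conclusion does not extend to the log-binomial analysis of perceived change.

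**What to change.** In Statistical analysis, state that the linear model for each secondary continuous outcome includes KL grade (three categories), as the stratification factor, in addition to the baseline value of that outcome. The abstract's description of the adjustment should be brought into line with that list at the same time.

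The cost is one sentence and two degrees of freedom per model (85 to 83 with 88 analysed). KL grade is known for every participant before allocation, so no data need be added.

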## Discussion

This study uses a single-blind randomised controlled trial design to investigate whether strengthening of the hip abductor and adductor muscles for 12 weeks in people with medial knee OA and varus malalignment reduces the knee adduction moment during walking gait. As a secondary aim, it will evaluate whether hip muscle strengthening also improves disease-associated symptoms, namely knee pain and physical function.

Lower limb muscle strengthening has recently received increased interest as an inexpensive treatment for knee OA due to its ability to reduce knee pain and improve physical function [23], and also because of its potential ability to reduce knee joint load. The novelty of the present study is the focus on hip strengthening. The hip muscles, particularly the abductors, play an important role in stablization of the pelvis and trunk. Indeed, movement of the contralateral pelvis or lateral leaning of the trunk over the stance limb, which may occur as a result of hip muscle weakness, has been suggested to adversely influence the magnitude of the knee adduction moment [26]. Thus, hip muscle activity appears to be an important, yet understudied, contributor to knee joint load.

We have chosen a series of six exercises to strengthen the hip abductors and adductors based on ease of performance and isolation of the targeted musculature. We have purposely avoided any exercises that involve components of internal or external rotation or that require muscles other than the abductors or adductors as the prime mover. It is acknowledged that human gait requires movement and stabilization in all three planes of movement, but we have focused on only the frontal plane given the established importance of kinematics and kinetics in this plane on knee OA pathophysiology [13,44].

Some authors propose that gait biomechanics in people with knee OA may be influenced by KL grade [45], suggesting a possible confounding influence of disease severity on the effects of interventions in this patient population. Thus, we will recruit equal numbers of participants with mild (KL grade 2), moderate (KL grade 3), and severe knee OA (KL grade 4) and perform post hoc exploratory subgroup analyses. Indeed, a potential benefit of our design is the identification of groups of patients in which conservative treatment such as hip muscle strengthening may or may not be beneficial.

The peak external knee adduction moment was chosen as the primary outcome measure in this study due to its association with medial compartment knee joint load and knee OA progression [11,15]. Thus, it represents a non-invasive, functional means to quantify knee joint loading and serves as a biomarker for disease progression [46]. Given the design of the study, measurement of muscle strength also constitutes an important outcome measure. To ensure that strength gains are limited to the hip abductors and adductors, measurement of hip flexion, extension, rotation (both internal and external), and knee extension will also be conducted. Isometric muscle strength measured with isokinetic and handheld dynamometry have both been shown to be valid and reliable in a clinical setting [47]. Lastly, objective and self-report measures of function, as well as self-reported measurement of pain will provide clinically relevant estimates of change in knee OA symptoms with our novel hip strengthening intervention. Therefore, this study will quantify the effects of hip strengthening on biomechanical, functional, and clinical attributes of knee OA.

It is anticipated that testing of all participants will be completed by the end of 2008. The results from this trial will contribute to evidence based recommendations for the usefulness of hip muscle strengthening in the management of medial knee OA.
